### 30.2. Biomarker substudy to assess the effect of RIC on MI size (48 hr AUC)

A major secondary endpoint of the ERIC-PPCI study will be MI size as measured by 48 hr AUC high-sensitive Troponin T and CK-MB. To date the effect of RIC on this specific endpoint has not been investigated. Using 72 hr AUC Trop I, Thibault et al demonstrated that ischaemic postconditioning reduced MI size from 24.6 (SD 20.6) x10^4 to 13.0 (SD 7.0) x10^4 IU/L. This equates to a relative reduction in MI size of 47%. In order to demonstrate a more conservative 25% relative reduction in MI size with RIC in PPCI patients from 24.6 (SD 20.6) x10^4 using 48 hr AUC hsTrop T with 80% power and at the 5% significance level, will require 177 patients in each treatment group or 354 patients in total. Allowing for 10% dropout rate would require 400 patients in total.

In view of the clear positive skewness of the Troponin AUC it is anticipated that this outcome will be analysed on the log scale. This will lead to estimation of the relative reduction in the MI size, which is expected to be a more precise estimate of any treatment effect. Therefore, the planned sample size of 400 patients is likely to provide greater than 80% power and allow for larger than a 10% loss in outcomes due to incomplete Troponin AUCs.

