| Echocardiography                       |                    |         | X              | X         |
| Electrocardiography                    | X                  |         | X  |           |
| Quality of life
(EuroQol EQ-5D-5L)  | X                  |         |                | X         |

 Blood samples for Ck and TnT drawn acute, 6-8 ( $\pm$ 4), 24 ( $\pm$ 8) and 48-72 (+6) hours post-PCI. Samples will be analyzed immediately.

 Research assistant complete the electronic case record form. Information regarding re-hospitalisation or death will be drawn from (electronic) patient chart.

 Echocardiography (sonogram of the heart, performed at day one to three and three to six months after-pPCI)

 Electrocardiography will be measure acute (admitting ECG), just prior to pPCI and 90 minutes post-PCI

 Quality of life (EuroQol EQ-5D-5L) at 6-8 weeks and 12 months via printed copy or via internet based questionnaire.

pPCI incl. the use of stents and antithrombotic regimens will be performed according to standard procedures at the treating hospital.

Blood samples will be drawn according to standard routine; no extra biomarkers will be measured. An extra sample of 15 ml will be drawn 72 H post pPCI. All blood samples will be analysed immediately. We will not establish a bio bank.

In Denmark, we will draw information regarding re-hospitalisation for hearth failure, AMI, revascularisation, or death from the (electronic) patient chart.

The Quality of life questionnaire (EuroQol EQ-5D-5L) will be performed as a sub-study on app. 400 patients. The patients will after the acute pPCI treatment be asked for the capacity to fill in the questionnaire via a printed copy or via a secured individual internet based access.

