#### ○ Cardiac Biomarkers Substudy

Values of high-sensitivity troponin T will be converted into a 48 hour area under the curve (AUC) summary measure for analysis. Differences in the mean AUC together with 95% confidence intervals will be calculated using a linear regression model. Troponin T will be collected at admission and 6-8, 24, and 48-72 hours post-PPCI in CONDI-2, and at admission and 6, 12, 24 and 48 hours post-PPCI in ERIC-PPCI. Where necessary, multiple imputation by chained equations will be used to account for missing information. Separate imputation models will be used for each trial. In CONDI-2, the troponin T measurement at 48-72 hours post-PPCI will be split in to those occurring at 48 hours (between 36 and 60 hours after the admission measurement) and those occurring at 72 hours (between 60 and 84 hours after the admission measurement) before multiple

imputation on all measurements up to 72 hours post-PPCI is performed. In ERIC-PPCI, multiple imputation on all measurements up to 48 hours post-PPCI will be performed. Twenty imputed datasets will be generated separately for each trial before being combined. The estimated difference in mean 48 hour AUC between the two treatment groups will be calculated using Rubin's rules. The distribution of the outcome variable will be investigated for non-normality and if necessary a data transformation will be made or a non-parametric statistical analysis will be conducted.

The following variables will be included in the multiple imputation models: troponin-T at each time point; treatment group; country (CONDI-2 only); gender; baseline age, diabetes, hypertension, systolic blood pressure, Killip class, and body weight; use of aspirin,  $\beta$ -blockers, nitrates, diuretics, Clopidogrel, Ticagrelor/Brillique, and metformin at admission for PPCI; previous myocardial infarction; peripheral vascular disease and hypercholesterolaemia at admission for PPCI; call to balloon time; pre/peri-procedural use of nitrates; length of index hospitalisation; and cardiac death within 12 months.

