CK-MB will be analysed using data from the CONDI-2 trial only. Values of CK-MB will be converted into a 48 hour AUC summary measure for analysis. Where necessary, multiple imputation by chained equations will be used to account for missing information (as described for troponin T). The estimated difference in mean 48 hour AUC between the two treatment groups will be calculated using Rubin's rules. The distribution of the outcome variable will be investigated for non-normality and if necessary a data transformation will be made or a non-parametric statistical analysis will be conducted.

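### The SAP makes a raw mean difference the default for the pooled troponin AUC, with an undefined data-driven switch and no trial term, although the ERIC-PPCI protocol already expects a log-scale analysis

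*Supplement*

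**What the plan says.** **Troponin, SAP version 3, 5.6.** The default analysis is: "Differences in the mean AUC together with 95% confidence intervals will be calculated using a linear regression model". Missing values are filled by chained equations, separately in each trial, with twenty imputed datasets. The difference in mean AUC is combined by Rubin's rules. The distribution is then examined for non-normality, and "if necessary a data transformation will be made or a non-parametric statistical analysis will be conducted". The CK-MB paragraph repeats this clause.

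**Trial.** The General paragraph of the SAP stratifies by trial only in those analyses that say so. The Cox analyses say so. The troponin regression does not, and there trial enters only through the separate imputation models.

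**Sampling.** CONDI-2 samples at admission, 6-8, 24 and 48-72 hours. ERIC-PPCI samples at admission, 6, 12, 24 and 48 hours.

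**Protocol.** ERIC-PPCI version 5, section 30.2, sizes the substudy on the raw scale and then states: "In view of the clear positive skewness of the Troponin AUC it is anticipated that this outcome will be analysed on the log scale". It expects this to give a relative reduction, estimated more precisely, with more than 80% power.

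**CK-MB.** The SAP states: "CK-MB will be analysed using data from the CONDI-2 trial only". CONDI-2 version 10 names creatine kinase (spelled creatinine kinase there) as its infarct-size endpoint in the synopsis and in the endpoint list. The footnote to its schedule reads "Blood samples for Ck and TnT drawn acute".

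**The concern.** A raw mean difference, a ratio of geometric means and a rank-based comparison are three different effect measures, and they can rank the arms differently when the spread differs between arms. The SAP leaves the choice until the outcome has been inspected. It sets no rule for when a change is needed and does not say that the inspection is blind to arm. The skewness was known at planning, so nothing has to be learned from the data to settle the scale.

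Two gaps make the plan hard to carry out as written. Rubin's rules are given for the mean difference only, and the SAP does not say how a non-parametric result would be combined over twenty datasets. The regression also pools AUCs built on different time grids (CONDI-2 has no 12-hour sample) without allowing the level to differ by trial.

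At stake is how clearly the infarct-size result can be read. ERIC-PPCI calls it a major secondary endpoint, and it is the mechanistic evidence beside the clinical outcome. The primary analysis is not affected.

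**Working it through.** **Inputs** (ERIC-PPCI version 5, 30.2): control AUC mean 24.6, SD 20.6 (×10⁴); effect "a more conservative 25% relative reduction in MI size with RIC in PPCI patients"; "with 80% power and at the 5% significance level"; 177 per arm. Two-sided testing is assumed, because it reproduces the stated size. (1.960 + 0.842)² = 7.849.

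1. **The plan's own figure.** Difference 0.25 × 24.6 = 6.15. With SD 20.6 in both arms, n = 2 × 20.6² × 7.849 / 6.15² = 176.1, rounded up to 177 per arm or 354 in total. 354 / 0.9 = 394, which the protocol rounds to 400. The stated size is reproduced. Power at 177 is 80.2%.

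2. **Log scale.** The protocol gives only a mean and SD, so an assumption is needed: log-normal AUC with equal coefficient of variation (CV) in both arms, 20.6 / 24.6 = 0.837.
   - Log-scale variance = ln(1 + 0.837²) = 0.531, so SD = 0.729.
   - Effect = |ln 0.75| = 0.288.
   - n = 2 × 0.5314 × 7.849 / 0.2877² = 100.8, so 101 per arm.
   - Power at 177 is 96.0% (96.1% in 20,000 simulated trials).

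3. **Raw scale under the same assumption.** Equal CV gives a treated SD of 0.75 × 20.6 = 15.45.
   - Mean variance = (424.36 + 238.70) / 2 = 331.5.
   - n = 2 × 331.5 × 7.849 / 6.15² = 137.6, so 138 per arm.
   - Power at 177 is 88.8% (89.9% simulated).

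4. **When the treated arm is less variable.** The postconditioning study cited in 30.2 had a treated mean of 13.0 and SD of 7.0, a CV of 0.538. Its log-scale variance is ln(1 + 0.538²) = 0.255, and the average over arms is (0.531 + 0.255) / 2 = 0.393.
   - *Arithmetic mean 25% lower.* The log difference shrinks to 0.288 − (0.531 − 0.255) / 2 ≈ 0.149, a geometric mean only about 14% lower. The log scale needs 2 × 0.393 × 7.849 / 0.1493², about 277 per arm. On the raw scale the treated SD is 0.538 × 18.45 = 9.93, the mean variance is 261.5 and n is 109.
   - *Geometric mean 25% lower.* The log scale needs 2 × 0.393 × 7.849 / 0.2877² = 74.5, so 75 per arm.

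| Assumption (log-normal) | Log, n per arm | Raw, n per arm |
|---|---|---|
| Equal CV 0.837 | 101 | 138 |
| Treated CV 0.538, arithmetic mean 25% lower | 277 | 109 |

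The direction of the gain therefore depends on the spread in the treated arm and on which mean is reduced. All these figures concern the ERIC-PPCI substudy of 400. The SAP states no number for the pooled troponin analysis.

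**The case against.** The best defence is that the SAP is loose here but not at odds with the protocol. The log scale is only anticipated in 30.2, and section 41.2 of the same protocol plans differences in means by linear regression for continuous outcomes and leaves detail to the SAP. A log transformation is among those the SAP permits, and a mean difference in several hundred patients is a legitimate effect measure. That stands: the fault is that the log scale is neither primary nor governed by a rule.

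A reader might infer more than the documents support:

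- **That the log scale lifts power from 80% to 96%.** The 80% uses one SD for both arms and the 96% uses one CV. On a common assumption the gain is about 7 points.
- **That omitting trial biases the comparison.** Both trials randomise in blocks stratified by centre, so arms should be balanced within trial, and each sampling grid affects both arms of its trial alike. The SAP also splits the CONDI-2 late sample into 48 and 72 hours.
- **That imputation will produce negative troponin values.** The SAP does not state the imputation scale or model, and predictive mean matching would avoid them.
- **That no non-parametric result can be pooled.** A rank-test p-value alone offers Rubin's rules nothing to combine, but a non-parametric estimate with a standard error can be pooled. The SAP is silent on this.
- **That CK-MB is taken from the wrong trial.** Restriction to CONDI-2 is an explicit choice, and the documents do not show which assay was run or whether ERIC-PPCI holds usable CK-MB data. Only an unreconciled label is shown.

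**Conclusion.** The point holds as one of pre-specification. For an outcome whose skewness was known, the SAP starts on the raw scale and lets the observed distribution choose among effect measures without a criterion. It gives no pooling method for one of the routes, and it merges two differently sampled trials without a trial term.

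Under log-normal AUC with equal CV, the log scale has about 96% power at 177 per arm against about 89% on the raw scale. The case for the log scale rests more on the protocol's stated expectation and on fixing the effect measure in advance than on this gain, which can reverse if the treated arm is less variable. The missing trial term costs precision and breaks with the trial-stratified Cox analyses, without necessarily causing bias. The CK and CK-MB wording is a separate inconsistency between documents.

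**What to change.** In SAP 5.6:

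1. Make log(48-hour troponin T AUC) the outcome of a linear model with treatment and trial, fitted in each imputed dataset and pooled by Rubin's rules. State the scale on which troponin is imputed.
2. Report the ratio of geometric means with its 95% confidence interval. Keep the raw mean difference as a sensitivity analysis.
3. Delete the switch clause in both the troponin and the CK-MB paragraphs.
4. State which assay CONDI-2 ran, CK or CK-MB, and align the SAP with CONDI-2 version 10.

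Admission troponin is better left out of the model. CONDI-2 randomises preferably in the ambulance, so that sample may follow the start of conditioning, and it is also the first point of the AUC.

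The cost is SAP wording only. The downside is that the effect is reported as a ratio instead of an absolute difference, which the sensitivity analysis still supplies.

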## Appendix: Figures

Figure 1: Trial flow diagram ERIC-PPCI

[figure not shown]

Figure 2: Trial flow diagram CONDI 2

[figure not shown]

### CONDI-2/ERIC-PPCI Summary of Statistical Analysis Plan Changes

| Version number | SAP Date      | Approved date  | Changes from previous version                                                                                                                                                                                                                                                                                                                                       |
|----------------|---------------|----------------|---------------------------------------------------------------------------------------------------------------------------------------------------------------------------------------------------------------------------------------------------------------------------------------------------------------------------------------------------------------------|
| 1.5            | 17 May 2018   | 10 August 2018 | Initial approved version of the SAP. Version 1 was never moved out of draft.                                                                                                                                                                                                                                                                                        |
| 2              | 9 April 2019  | 10 April 2019  | 
The following changes were made to the SAP:
 
 
- Clarified that data will be supplied as STATA files
 
- Was expanded to include substudy analysis.
 
- Clarified that the analysis would be stratified by trial.
 
- Added details for the analysis of the cardiac biomarkers substudy.
 
 |
| 3              | 12 April 2019 | 15 April 2019  | 
The following changes were made to the SAP:
 
 
- It was clarified that MACCE was included in the survival analysis of the clinical outcomes.
 
- Repeat HHFs alone will be analysed.
 
- The analysis of device implantation was detailed.
 
                                                      |
